### Blood measurements

After an overnight fast, blood samples are obtained to measure lipid spectrum (cholesterol, HDL-cholesterol, LDL-cholesterol, triglycerides) liver function (y-GT, ALAT, ASAT) and C-reactive protein (CRP), haemoglobin, hematocrite, MCV, ferritin and HbA1C. In patients with a triglyceride level ≤ 4.5 mmol/l, LDL-cholesterol is calculated using the formula of Friedewald. Since this calculation is unreliable in patients with a triglyceride level > 4.5 mmol/l, LDL-cholesterol is measured directly in these patients using a Roche Cobas 6000 chemical analyzer. The method for this direct measurement is an enzymatic reaction with the transformation of LDL-cholesterol in a color product. High sensitive CRP measurement is performed turbidimetrically with a Roche Cobas 6000 chemical analyzer. To determine glucose tolerance and insulin resistance, the participants are given glucose, in a dose of 1.75 g per kilogram of body weight (up to a maximum of 75 g) orally. Blood samples are obtained at 0 and 120 minutes for the measurement of glucose and insulin levels. In accordance with the American Diabetes Association guidelines, impaired fasting glucose is defined as a fasting plasma glucose level between 5.6 - 6.9 mmol/l and impaired glucose tolerance as a 2-h postload glucose level in the oral glucose tolerance test (OGTT) between 7.8-11.0 mmol/l. Diabetes is defined as a fasting plasma glucose level of ≥ 7.0 mmol/l or a 2-h postload glucose level in the OGTT of ≥ 11.1 mmol/l [22].

### Quality of life

Quality of life is measured using the EQ-5D [23]. The EQ-5D questionnaire contains a descriptive system of health related quality of life consisting of five dimensions (mobility, self-care, usual activities, pain/discomfort, and anxiety/depression). For each dimension there are three levels of severity (no problems/some or moderate problems/extreme problems). A standard vertical 20 cm visual analogue scale is also included to measure an individual's direct valuation of their current health-related quality of life state. Utilities will be estimated using the Dutch tariff [24]. Quality Adjusted Life Years (QALYs) will be calculated by multiplying the utilities with the amount of time a participant spent in a particular health state. Transitions between health states will be linearly interpolated.

### Cost measures

Cost calculations will be based on actual resource use, using prospective data collection during 2 years (the 12 months intervention period and the 12 months follow-up) through cost diaries. The costs of the interventions (inpatient care and recurrent return visits of 2 days) will be estimated using a bottom-up approach. Other costs include direct healthcare costs (e.g. costs of visits to the general practitioner, internist, physiotherapist, inpatient period), direct non-healthcare costs (informal care provided by parents and legal guardians and travel costs), and indirect costs (costs related to loss of productivity of the parents and legal guardians). Cost diaries are formatted as calendars on which health care utilization can be registered. The calendars will be sent to the families every 3 months. After 3 months the calendars will be returned by the parents, using stamped envelopes, also if there has been no health care utilization during that period. In case a calendar is not returned, use of health care will be inventoried by telephone calls and/or e-mails.

If available, standard costs recommended by the Dutch Health Insurance Council will be used to value resource use [25]. Medication costs will be valued using prices of the Royal Dutch Society of Pharmacy [26].

### Sample size calculation

Based on a previous study comparing intensive inpatient treatment with an ambulatory treatment in the same treatment centre it is calculated that 40 participants in both intervention groups are sufficient to detect a 0.5 SDS-BMI difference between the two groups after one year (with α = 0.05 and power = 0.8). Based on earlier experience in the same setting and with similar participants it is feasible to recruit these numbers of participants.

### Statistical analyses

An intention-to-treat analysis will be performed. A per protocol analysis will also be performed after careful description of correlates of non-adherence and dropout.

To take into account the repeated measurements over time, we will use generalized estimating equations for panel data analysis, also known as cross-sectional time-series analysis, with the use of the Stata software XTGEE command; this will allow us to account for the non-independence of repeated measurements of the same bio-indicator in the same participant over time. Linear regression will be applied for continuous outcomes and logistic regression for dichotomous outcomes. We will use age, sex, time point, and intervention group as explanatory variables in our models.

An economic evaluation from a societal perspective will be conducted alongside the randomized controlled trial. Multiple imputation will be used to impute missing cost and effect data. Five imputed data sets will be created, each of which will be analyzed separately. The results of these five analyses will be pooled using Rubin's rules [27].

Costs generally have a highly skewed distribution. Therefore, bootstrapping with 5000 replications will be used to estimate "approximate bootstrap confidence" (ABC) intervals around cost differences [28,29]. Incremental cost-effectiveness and cost-utility ratios will be calculated by dividing the difference in total costs between the groups by the difference in SDS-BMI and QALYs, respectively. Non-parametric bootstrapping will also be used to estimate the uncertainty surrounding the incremental cost-effectiveness and cost-utility ratios (5000 replications). The bootstrapped cost-effect pairs will be plotted on a cost-effectiveness plane (CE plane) [30] and used to estimate cost-effectiveness acceptability curves (CEA curves). CEA curves show the probability that the intervention is cost-effective in comparison with usual care for a range of ceiling ratios. The ceiling ratio is defined as the amount of money society is willing to pay to gain one unit of effect [31].

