## Methods/Design

### Design

This study is designed as a randomized controlled clinical trial with three study arms. The cost-effectiveness of two intensive one-year treatments that vary in inpatient period length and usual care for severely obese children and adolescents will be evaluated. There is a one year follow-up after treatment. Participants who meet the inclusion criteria and consent to participate in the study will be randomized to one of the three study arms (described under 'interventions'). Because of the nature of the treatments evaluated in this study, parents and participants as well as professionals at Heideheuvel and in the usual care condition cannot be blinded to the type of intervention. A table of random numbers is used to randomize participants. At the beginning of the first year 40 (13-18 years) participants are randomized into: group A (10), group B (10) or group C (20). The participants in group C will be randomized into group A (10) or B (10) after one year of receiving usual care. This process is repeated for another 40 participants (8-13 years) after 6 months. At the end of the fourth year all 80 participants (40 in each inpatient treatment group) will have completed the program and 1 year of follow up (Figure 1). Data collection started in August 2009 and will continue until July 2013. The Medical Ethics committee (METc) of VU University Medical Centre approved the study design, protocol and informed consent procedures.

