#### Phase 1 (weeks 1-6 for treatment A, weeks 1-8 for treatment B)

During the first phase extensive physical and psychosocial examinations are carried out. The children are medically examined and they have several individual appointments with among others the dietician and psychologist, both with and without their parents, to assess what the problem areas are for each child. During this period the children receive schooling at a study centre at Heideheuvel, except for the primary school children. They go to primary schools in the neighborhood where the teachers can monitor dietary habits of the children. A very important secondary goal in this phase is also the group formation.

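### The GEE has no term for the intake groups of about ten in which both inpatient programmes are delivered; if outcomes correlate within groups, A-versus-B standard errors are too small

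*Protocol article*

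**What the plan says.** **Intakes (protocol article, Design).** "At the beginning of the first year 40 (13-18 years) participants are randomized into: group A (10), group B (10) or group C (20"). A year later, "The participants in group C will be randomized into group A (10) or B (10) after one year of receiving usual care". Then "This process is repeated for another 40 participants (8-13 years) after 6 months". At the end, "all 80 participants (40 in each inpatient treatment group) will have completed the program". Each inpatient arm is thus made up of four intakes of ten, eight in all.

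**Delivery in groups.** Under Interventions, all children stay overnight at the clinic during the inpatient phase and the return visits. Phase 1 says "A very important secondary goal in this phase is also the group formation". Phases 2 and 3 describe group education, and Phase 4 says that two group coaches are on hand throughout the day. In Table 1, exercise, the parents' course and the education and activity rows are marked as group sessions in both arms.

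**Analysis (Statistical analyses).** The model is a GEE fitted with XTGEE, of which the article says "this will allow us to account for the non-independence of repeated measurements of the same bio-indicator in the same participant over time". The explanatory variables are age, sex, time point and intervention group. Neither treatment group nor wave is among them.

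**Sample size (Sample size calculation).** "40 participants in both intervention groups are sufficient to detect a 0.5 SDS-BMI difference between the two groups after one year". The significance level is given as 5% and the power as 80%. No SD, ICC or design effect is given.

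**The concern.** Children who live, train and are coached together, in a programme that sets out to form a group, may end up with more similar SDS-BMI changes than children drawn from different groups. This similarity arises after allocation, so individual randomisation does not remove it. A GEE whose correlation structure is confined to the participant does not capture it, and a robust variance clustered on the participant would not either.

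The consequence falls mainly on A versus B. Programme B was developed to match A in effect at lower cost and with less disruption to the family, so the width of that interval bears on the main policy question. An interval that is too narrow could present a difference between a few particular groups as a difference between programmes.

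**Working it through.** **Inputs from the article.** Group size m = 10 and four groups per inpatient arm (Design). Difference 0.5 SDS-BMI, n = 40 per arm, α = 0.05, power 0.8 (Sample size calculation).

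**Assumptions.** Two-sided test (the article does not say). ICC of 0.02, 0.05 or 0.10, the same in both arms and wholly specific to the treatment group. No dropout.

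**1. The plan's own figure.** Without an SD, 40 per arm cannot be strictly reproduced, so I solved for the SD under independence: SD = 0.5 / [(1.960 + 0.842) × √(2/40)] = 0.798 (0.788 by noncentral t). An SD of 0.80 gives 41 per arm. The stated 40 is consistent with an ordinary unclustered two-sample calculation, but this does not prove that one was used.

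**2. A versus B.** Design effect DE = 1 + (10 − 1) × ICC. The true SE is √DE times the naive SE. Effective n = 40/DE. True error of a nominal 5% test = 2 × [1 − Φ(1.96/√DE)].

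| ICC (assumed) | DE | SE multiplier | Effective n per arm | True error |
|---|---|---|---|---|
| 0 | 1.00 | 1.00 | 40 | 5.0% |
| 0.02 | 1.18 | 1.09 | 33.9 | 7.1% |
| 0.05 | 1.45 | 1.20 | 27.6 | 10.4% |
| 0.10 | 1.90 | 1.38 | 21.1 | 15.5% |

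In 20,000 simulated trials per ICC, with four groups of ten per arm and an ordinary t test, the error was 5.1%, 7.2%, 10.4% and 15.8%.

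**3. A or B versus usual care.** Only one side is grouped. With 40 against 40, treated as separate children, the variance inflation is (DE + 1)/2.

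- ICC 0.05: (1.45 + 1)/2 = 1.225, error about 8%.
- ICC 0.10: (1.90 + 1)/2 = 1.45, error about 10%.

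**4. Power for 0.5 SDS-BMI, if the 40 assumed independence.** Power = Φ(0.5 / [SD × √(2 × DE/40)] − 1.96).

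| ICC (assumed) | Normal approximation, SD 0.798 | t test, SD 0.788 | Group-level t test, 6 df, SD 0.798 |
|---|---|---|---|
| 0 | 80% | 80% | 65% |
| 0.02 | 73% | 73% | 58% |
| 0.05 | 64% | 64% | 50% |
| 0.10 | 53% | 52% | 40% |

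The last column is the price of inference from eight groups (8 − 2 = 6 df). It applies even at ICC 0.

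**The case against.** **The sentence on GEE is correct, and a condensed article may leave therapy-group clustering to a fuller document.** The sentence is indeed correct as a description of GEE. But the article goes beyond silence: it names the method, the correlation handled and the covariates, and that model treats children in one group as independent.

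**The size is assumed.** This stands. The article gives no ICC; at ICC 0 there is no error, and at 0.01 the SE multiplier is only 1.04. A reader might infer that the standard errors are shown to be too small. The article supports only the conditional statement.

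**The groups may be looser than they look.** This stands in part. A reader might infer closed groups from the batch randomisation and fixed-week phases, but the article does not say whether late entry or replacement is allowed. Exposure also differs by arm: B children go home after two months, A children attend a nearby school from phase 2, and primary school children attend outside schools throughout phase 1. One common ICC for both arms is a simplification.

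**Some group variance is shared.** A and B of one intake run at the same time in the same clinic, and nothing says that each has its own staff. Staff, season and intake effects common to both cancel in A versus B, and age in the model absorbs some of the difference between age bands. The figures therefore apply to the part of the ICC specific to a treatment group. Peer and group-dynamic effects remain.

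**The power argument is circular.** A reader might infer that the 80% is overstated. With no SD or formula given, and the SD back-solved under independence, the article does not show this. The loss of power can only be stated conditionally.

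**Conclusion.** The point holds in conditional form. Delivery in eight intake groups of about ten is well supported by the article, and the stated GEE does not allow for it. Under any positive correlation specific to the treatment group, the A-versus-B intervals are too narrow and the p-values too small. Over the assumed ICC range of 0.02 to 0.10, the SE is understated by a factor of 1.09 to 1.38. A reader might carry the A-versus-B error rates over to the comparisons with usual care. That is not supported, because usual care is not delivered in these groups and the inflation there is smaller. The power figures rest in addition on an independence assumption that the article neither states nor rules out, and they precede any loss from few degrees of freedom. The issue should be settled before analysis, but it does not invalidate the design.

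**What to change.** **Statistical analyses.** Pre-state a sensitivity analysis of the A-versus-B contrast with treatment group (arm by age cohort by wave, eight groups) as a random effect and small-sample degrees of freedom. Keep the participant-level correlation, so that children who move from usual care into A or B remain linked to their own earlier measurements. Report the ICC with its uncertainty. Do not rely on GEE sandwich errors at group level, which would be unreliable with eight groups.

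**Sample size calculation.** State that the 80% power assumes no correlation within treatment groups, or give the SD and ICC that were used.

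**Economic evaluation.** Resampling whole groups is not a sound replacement for the planned bootstrap: four groups per arm allow only C(7,4) = 35 distinct resamples per arm.

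**Cost.** Analysis wording only, with no change to conduct or data collection. The price is a wider interval, an imprecisely estimated ICC and low power on about 6 df, which is why this belongs in a sensitivity analysis and not in the primary one.

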### Measurements

Primary outcome measure is (SDS) BMI. Secondary outcomes are quality of life and cardiovascular risk factors like blood pressure, bodily circumferences, serum lipids, glucose levels and insulin levels. Eating behavior and physical activity are also assessed. The EuroQoL (EQ-5D) is used to measure quality of life and to calculate Quality Adjusted Life Years (QALYs) over the follow-up period of 24 months. Measurements will be done at four points in time: at baseline (start of treatment) and after 6, 12 and 24 months.

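### The listed GEE covariates yield one visit-averaged group effect, which is neither the one-year A–B difference the trial is sized on nor able to separate it from maintenance at 24 months

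*Protocol article*

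**What the plan says.** All references are to the protocol article.

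- **Outcome and visits (Measurements).** "Primary outcome measure is (SDS) BMI". "Measurements will be done at four points in time: at baseline (start of treatment) and after 6, 12 and 24 months".
- **Target (Sample size calculation).** "40 participants in both intervention groups are sufficient to detect" the effect, and the calculation is described as "sufficient to detect a 0.5 SDS-BMI difference between the two groups after one year", "with α = 0.05 and power = 0.8". No SD is given.
- **Model (Statistical analyses).** "we will use generalized estimating equations for panel data analysis, also known as cross-sectional time-series analysis", run with the Stata XTGEE command. The covariates follow: "We will use age, sex, time point, and intervention group as explanatory variables in our models". No section mentions an interaction or adjustment for the baseline outcome.
- **Aims (Discussion).** The study is meant to show both the effect of a year of treatment and whether it lasts a year after treatment ends.
- **Usual care (Design; Interventions).** Group C has usual care for one year and is then randomised to A or B.

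**The concern.** The trial asks two visit-specific questions: the A–B difference at 12 months, and what remains of it at 24 months. A model with group and visit as separate terms assumes that the group difference is the same at every visit and returns one number for it. If the difference changes over time, that number answers neither question.

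The baseline visit can make this worse. Randomisation makes the expected group difference at baseline zero, so a baseline row among the outcomes pulls the average down. Baseline SDS-BMI is not listed as a covariate either, so chance imbalance at entry adds noise that could be removed.

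At stake are the size of the primary effect, the power of its test, and the ability to report maintenance at all.

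**Working it through.** **Inputs.** From the article: 40 per intervention group, a difference of 0.5, alpha 0.05, power 0.80, and visits at 0, 6, 12 and 24 months. Assumed: a two-sided test, complete data, equal SD at all visits, a common within-person correlation r of 0.5 to 0.8, and an independence or exchangeable working correlation (the article names none).

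**Step 1: the plan's own figure.** The SD is not stated, so 40 per group cannot be reproduced independently; it can only be inverted. A two-sample t-test with 40 per group has 80% power for 0.5 if the SD is 0.788 (0.79 rounded). The normal approximation gives 0.5 × √20 / (1.960 + 0.842) = 0.798. I use 0.788 below; 0.798 lowers the powers by about one percentage point or less.

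**Step 2: what the coefficient estimates.** Let d0, d6, d12 and d24 be the true A–B differences in absolute size. With baseline as an outcome row:

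- coefficient = (d0 + d6 + d12 + d24) / 4, with d0 = 0 in expectation
- SE = SD × √(2/40) × √((1 + 3r)/4)

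With baseline left out of the outcome rows:

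- coefficient = (d6 + d12 + d24) / 3
- SE = SD × √(2/40) × √((1 + 2r)/3)

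For a 12-month contrast adjusted for baseline: SE = SD × √(2/40) × √(1 − r²).

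Power is Φ(effect/SE − 1.96).

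**Step 3: results for a true 12-month difference of 0.5.**

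| Model | Differences at 6, 12, 24 months (assumed) | Estimates | SE, r = 0.5 to 0.8 | Power, r = 0.5 to 0.8 |
|---|---|---|---|---|
| Listed terms, baseline an outcome row | 0.5, 0.5, 0.5 | 1.5/4 = 0.375 | 0.139 to 0.163 | 77% to 64% |
| Listed terms, baseline an outcome row | 0.3, 0.5, 0.25 | 1.05/4 = 0.26 | 0.139 to 0.163 | 47% to 37% |
| Listed terms, follow-up rows only | 0.5, 0.5, 0.5 | 1.5/3 = 0.50 | 0.144 to 0.164 | about 93% to 86% |
| Listed terms, follow-up rows only | 0.3, 0.5, 0.25 | 1.05/3 = 0.35 | 0.144 to 0.164 | 68% to 57% |
| 12-month contrast, baseline-adjusted | either | 0.50 | 0.153 to 0.106 | 91% to over 99% |

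**Step 4: check by simulation.** GEE with exchangeable correlation was run 400 times per profile, with SD 0.798 and r = 0.8. For 0.5, 0.5, 0.5 the main-effects coefficient averaged 0.37, with power 63%. For 0.25, 0.5, 0.25 it averaged 0.27 (formula: 1.0/4 = 0.25), with power 35%. Adding group-by-visit terms, the 12-month interaction averaged 0.51 and 0.50, with power 99% in both.

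**Step 5: usual care.** Group C has no usual-care value at 24 months. With baseline as an outcome row, a sustained 0.5 difference between A and C becomes (0 + 0.5 + 0.5)/3 = 0.33. The A–B and A–C coefficients would then average over different sets of visits.

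**The case against.** The strongest reply is that one sentence in a condensed article names variables, not every model term. It gives no equation, does not exclude an interaction and does not say which coefficient is primary. The Discussion's interest in both one year and maintenance suggests that visit-specific estimates were intended, and a fuller plan may contain them. This is fair as to intent. But the article does state a covariate list, and nothing in it leads from that list to the one-year contrast.

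Four stronger readings are tempting and are not supported:

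- **That baseline is certainly averaged in.** The article lists baseline as a measurement time, has time point as a covariate and has no baseline covariate, so this is the natural reading. It is nowhere stated. Without it, a constant 0.5 is recovered with more than the planned 80% power.
- **That the trial has only 37% to 47% power.** That needs baseline as an outcome row and an effect profile with no source in the article. It is an illustration only.
- **That the analysis is biased or its test invalid.** A visit-averaged difference is a different quantity, and its test of no effect remains valid. Chance baseline imbalance adds variance, not systematic bias.
- **That the cost-effectiveness ratios use raw differences.** The text forms them "by dividing the difference in total costs between the groups by the difference in SDS-BMI and QALYs" and is silent on adjustment.

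The SD and correlation are also assumptions. Entry thresholds on SDS-BMI could narrow the spread at baseline, so a common SD at all visits is a simplification.

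**Conclusion.** The concern holds in a limited form. As written, the model's single group coefficient is a visit average. It equals the one-year A–B difference only if baseline is not an outcome row and the effect is constant over follow-up. Under no reading can it separate the one-year effect from maintenance. This mismatch does not depend on any assumed SD or correlation.

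Its numerical size does depend on assumptions. With baseline among the outcomes, a sustained 0.5 is reported as 0.375, a 25% reduction, and power falls below the planned 80% to about 77% to 64% (SD 0.79, r 0.5 to 0.8, complete data). Without baseline among the outcomes, the harm is confined to effects that vary over time, such as 0.35 in place of 0.5 under the assumed profile.

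**What to change.** Replace the covariate sentence with a full model statement:

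- **Model:** SDS-BMI at 6, 12 and 24 months on group, categorical visit, group-by-visit, baseline SDS-BMI, age and sex.
- **Primary contrast:** A versus B at 12 months, matching the sample size calculation.
- **Maintenance contrast:** A versus B at 24 months.
- **Usual care:** limit contrasts with group C to 6 and 12 months, because group C is re-randomised after one year. State how participants who contribute first under usual care and then under A or B are handled.

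Optionally, state that the SDS-BMI and QALY differences in the ratios are adjusted for baseline SDS-BMI and baseline EQ-5D utility respectively.

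The change needs no new data, since baseline values are already collected. It costs a few sentences and a few model parameters. It should be fixed before outcome data are examined, because participants and staff are not blinded and the choice of contrast should not follow the results.

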A challenge of the study will be keeping the attrition rate to a minimum. The study population is expected to have a relatively low socioeconomic status (SES) and to present relatively many psychological problems and socially complicated family structures. This can interfere with adherence to the treatment program. The psychological characteristics of the patients and their parents will be described in a separate study. Another difficulty will be the recruitment of participants, because of the extended inpatient periods. Especially in the group of children aged 8-13, we expect problems with recruitment because an inpatient period of 2 or 6 months imposes a very heavy burden on families and children. Also, because recruitment is nationwide, part of the parents will have to travel quite a lot, since their active participation and frequent presence during treatment is required. This can lead to high work absenteeism for the parents or loss of vacation days which will also be measured.

For the calculation of %BF the adjusted equation by Kushner et al is used [20], since the original equation by Kushner et al is developed to calculate total body water and is therefore not applicable. We have chosen for this equation after careful consideration as there are more suitable equations to calculate %BF specifically developed for obese children and adolescents such as the equations of Lazzer et al [32] and Schaeffer et al[33]. However we are limited in our choice because only resistance (R) is recorded. Cost calculations will be based on actual resource use; therefore prospective data collection through cost diaries during 2 years is used. However, the risk of this type of data collection is drop out; the longer the participant are followed, the higher the chance of loss to follow up. Also, bias can be introduced with this type of data collection, since it is based on self reporting. People can forget to note absenteeism or visits to health care professionals, even with the use of the cost diaries. By prospectively collecting data we hope to get valid estimates of health care utilization.

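### Missing SDS-BMI is imputed for the economic evaluation, but the primary GEE analysis of SDS-BMI has no stated missing-data step and may be biased by outcome-related dropout

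*Protocol article*

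**What the plan says.** Both parts of the plan stand in the Protocol article, section Statistical analyses.

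- **Clinical analysis.** After naming an intention-to-treat analysis and a per-protocol analysis, the article states that "we will use generalized estimating equations for panel data analysis, also known as cross-sectional time-series analysis, with the use of the Stata software XTGEE command". The covariates are age, sex, time point and intervention group. Linear models serve continuous outcomes and logistic models serve dichotomous ones. No working correlation, weighting or imputation is named.
- **Economic evaluation.** The next paragraph opens: "An economic evaluation from a societal perspective will be conducted alongside the randomized controlled trial". Imputation comes directly after that sentence: "Multiple imputation will be used to impute missing cost and effect data. Five imputed data sets will be created", with pooling by Rubin's rules. The effects are identified a paragraph later, where the ratios are formed by "dividing the difference in total costs between the groups by the difference in SDS-BMI and QALYs, respectively".

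The Measurements section makes SDS-BMI the primary outcome, measured at 0, 6, 12 and 24 months. The Discussion says: "A challenge of the study will be keeping the attrition rate to a minimum". It gives no expected rate. It links adherence problems to low socioeconomic status, psychological problems and family circumstances, none of which is a model covariate.

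**The concern.** The primary outcome of the effectiveness analysis is also the effect in the cost-effectiveness ratio. If the economic analysis imputes missing SDS-BMI and the GEE takes the rows it has, the trial can report two different SDS-BMI differences for one comparison of arms.

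The GEE result rests on the stronger assumption of the two. In a weight programme, participants who fail to lose weight or who regain it may be more likely to leave. If this happens to a different degree in the arms, those who remain no longer represent the randomised groups. The Discussion also cites a review in which attrition was lower with inpatient treatment. Unequal dropout between arms with six months, two months and no inpatient stay is therefore plausible, though not shown.

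A bias towards zero would matter because the shorter programme (B) was developed in the hope that it would work as well as the longer one (A). A diluted difference would look like support for that hope.

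**Working it through.** **1. The plan's own figure.** The Sample size calculation gives 40 per intervention group for a difference of 0.5, alpha 0.05 and power 0.8. No SD is stated. Taking the test as two-sided, the implied SD is 0.5 / [(1.96 + 0.84) × √(2/40)] = 0.80. This point does not dispute the 40. The implied SD is used below.

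**2. When unweighted GEE is unbiased.** Two conditions suffice separately:
- dropout does not depend on earlier outcomes, given the model covariates; or
- the outcome is continuous with identity link, the working correlation is correct, and data are missing at random.

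The second condition does not carry over to the logistic models.

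**3. Size of the bias for SDS-BMI.** All of the following are assumptions, because the article gives no SD, correlation or dropout rate: SD 0.8, correlation 0.85 per 6 months (autoregressive), true difference 0.50 at 12 and 24 months, large samples, a separate mean for each group and visit. Dropout depends on the previous SDS-BMI, either as a level or as change from baseline.

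| Dropout driven by | GEE correlation | 12 months | 24 months |
|---|---|---|---|
| nothing (completely at random) | independence | 0.50 | 0.50 |
| nothing (completely at random) | exchangeable | 0.50 | 0.50 |
| level, same rule in both arms | exchangeable | 0.50 | 0.50 |
| level, one arm only | exchangeable | 0.48-0.49 | 0.54 |
| change, same rule in both arms | exchangeable | 0.49 | 0.47 |
| change, one arm only | exchangeable | 0.46 | 0.40 |
| level, one arm only | independence | 0.30 | 0.29 |

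A likelihood model with the correct covariance returned 0.50 in the scenarios with dropout on change (one arm or both) and on level in one arm.

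A more severe case of change-driven dropout in one arm kept 85% versus 67% at 12 months and 72% versus 39% at 24 months. Exchangeable GEE gave 0.405 and 0.343, against full-data values of 0.465 and 0.479 in the same simulation. The shortfalls are 0.465 − 0.405 = 0.06 and 0.479 − 0.343 = 0.14. A binary outcome under logistic GEE moved the same way: the 24-month log odds ratio was −0.74 instead of −1.02.

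With independence correlation the largest error came from exchangeable data (correlation 0.7) and level-driven dropout in one arm: 0.25 at 24 months, an error of 0.50 − 0.25 = 0.25. With exchangeable working correlation on those same data, which is then correct, the estimates were 0.49 and 0.50.

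**4. Scale.** With 40 per group and SD 0.8, the standard error of a difference is 0.8 × √(2/40) = 0.18 before any loss. A bias of 0.06 is 0.06/0.18 = one third of a standard error. A bias of 0.14 is 0.14/0.18 = 0.8 of one.

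**5. Five imputations.** The fraction of missing information (FMI) is assumed to be 0.3 to 0.4.
- Relative efficiency 1/(1 + FMI/5): 1/1.06 = 0.94 and 1/1.08 = 0.93.
- Rubin degrees of freedom 4/FMI²: 4/0.09 = 44 and 4/0.16 = 25.
- t multipliers 2.01 and 2.06 against 1.96, so intervals are about 3-5% wider.

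**The case against.** The strongest reply is that this is a condensed article. It nowhere says that the GEE uses observed data alone or that imputation is confined to the economic evaluation. Both are inferred from where the sentences stand and from how GEE treats absent rows. A full protocol or SAP may name the working correlation and the missing-data approach. Imputation also has its own purpose in the economic part, since bootstrapped cost-effect pairs need both values for every participant. The article further plans to describe correlates of dropout and to chase unreturned cost calendars by telephone or e-mail. All of this is fair, and it is why the point is not put as a contradiction. What remains is that the text fixes a method for each analysis and gives a missing-data step to only one, although both estimate the same SDS-BMI contrast. Describing dropout does not correct an estimate, and retrieving calendars restores costs, not SDS-BMI.

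Four stronger readings are tempting and should not be drawn:
- **That GEE needs dropout completely at random.** It does not; see step 2 of the working.
- **That the bias is about a quarter of an SDS unit.** That size requires independence correlation. The article names no structure, and it chose GEE in order to allow for correlated repeated measurements.
- **That outcome-driven, unequal dropout is expected here.** The article gives no rate and ties adherence problems to social and psychological factors, not to weight regain.
- **That five imputations is an error.** The loss is small.

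It is also fair that a bias of 0.01-0.06 at 12 months is modest beside a standard error of 0.18.

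**Conclusion.** The point holds as a matter of alignment and robustness. The article describes imputation of missing SDS-BMI only within the economic evaluation and gives the primary GEE analysis no missing-data step. With attrition anticipated, the effectiveness estimate may be biased and may differ from the SDS-BMI difference in the cost-effectiveness ratio.

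Under exchangeable correlation and dropout driven by earlier SDS-BMI, the bias on a true difference of 0.5 is about 0.01-0.06 at 12 months and 0.03-0.14 at 24 months. It is usually towards zero, but one scenario went the other way (0.54), and one with the same level-driven rule in both arms showed none. These sizes rest on the assumed SD, correlation and dropout models, and on a model with group-by-visit means, which the article does not spell out. The upper ends need severe, one-sided dropout. No sample-size figure changes. The change is worth making because a method with a weaker assumption is available at almost no cost.

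**What to change.** Either of two changes to the Statistical analyses section would do:

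1. For continuous outcomes, replace the GEE by a likelihood-based mixed model with visit as a factor, group-by-visit terms and an unstructured within-person covariance. This is valid under missing at random.
2. Keep the planned GEE, but run it on the same imputed data sets as the economic evaluation. Impute by arm, with baseline and earlier SDS-BMI in the imputation model. This route also serves the binary outcomes, which option 1 does not cover.

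Whichever is chosen, state that the effectiveness result and the cost-effectiveness ratio handle missing SDS-BMI under the same assumption.

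Optionally, raise the number of imputations from 5 to about 30-50 to reduce Monte Carlo error in the pooled intervals and curve probabilities.

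The cost is revised wording, a little more analysis work and minutes of computing time. No new data are needed.
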